### Estimation of the expected effect sizes and sample size

Based on results of the study of Rooke and colleagues
[23], we expect small to medium effect sizes for the reduction of the quantity of cannabis used and the frequency of cannabis use between study arm 2 (web-based self-help without chat counseling) and study arm 3 (waiting list control) of at least 0.15 (Cohen’s f) between t0 and t2. Assuming that the study arm 1 (web-based self-help with chat counseling) will result in a larger Cohen’s f, we rely on the aforementioned comparison (arm 2 vs. arm 3) for sample size estimation. A sample size of n = 89 in each study group would have 80% power (F-test, α = 5%) to detect this difference based calculations performed with the G-Power software. Thus, we aim to recruit a total of 267 participants.

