Studies of web-based programs for the reduction of the most frequently used illicit drugs, such as cannabis, cocaine and amphetamines, are scarce
[21,22]. Currently, there are only two specific web-based programs for the reduction of cannabis use that have been investigated in randomized controlled trials, and these programs employ different intervention approaches
[23,24]. The German “Quit the Shit” program
[24] is based on principles of self-regulation and self-control and is a solution-focused approach. This program is structured into weekly personalized feedback sessions based on participants’ consumption diary entries, intake and termination chats, and the total allowed program time is 50 days. Attrition in the German study of Tossmann and colleagues
[24] was high and higher in the intervention (11.6%) condition than in the waiting list control condition (24.7%). Nevertheless, these authors found significant effects on cannabis use reduction in their per-protocol and last observation carried forward analyses. The Australian program “Reduce Your Use: How to Break the Cannabis Habit”
[23] is a fully automated self-help intervention consisting of 6 modules for the amelioration of cannabis use disorders based on cognitive-behavioral therapy (CBT) approaches
[25,26], motivational interviewing (MI
[27]), and behavioral self-management (BSM
[28]). This program was tested for effectiveness in a randomized-controlled trial and compared to a psycho-educative control condition also consisting of 6 modules. Study retention was higher in the intervention and the control condition after 6 weeks (66% vs. 64%) and at a 3-month follow up (54% vs. 52%) than in the aforementioned German study
[24]. The frequency of cannabis use and the quantity of cannabis consumed were both more reduced in the intervention group than in the control group at 6 weeks and at the 3-month follow up.

The combination of a fully automated self-help intervention based on therapy approaches of the study of Rooke and colleagues
[23] with additional individual chat sessions for the reduction of cannabis use could potentially increase the effectiveness of interventions for problematic cannabis as has been demonstrated for the reduction of alcohol use in problematic alcohol users
[20]. More interactive web-based interventions may be more effective in reducing cannabis use in problematic cannabis users. However, the results of the Australian study

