## Methods/design

### Aims of the trial

This study aims to compare the effectiveness of a web-based self-help intervention alone or combined with chat counseling in the reduction of the cannabis use of problematic cannabis users via a three-arm randomized controlled trial. The primary outcome is the weekly quantity of cannabis consumed (measured in the number of standard joints per week) at the 3-month follow up. The secondary outcome measures include the frequency of cannabis use days (7 day point prevalence of cannabis use days), changes in problematic cannabis use, severity of cannabis dependence, cannabis withdrawal symptoms, cannabis craving, the use of other psychoactive substances, mental health symptoms, functional health states, intervention satisfaction, and treatment retention. The predictive validity of participant characteristics for treatment retention and primary and secondary outcomes will be explored.

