### Randomization and allocation

Once participants have completed their baseline assessment, they will be randomized by a computer program in a 1:1:1 ratio to 1 of 3 “parallel” groups, and this assignment will be automatically registered in the background database. As we offer full transparency on the three groups, we expect a certain risk that some might try to circumvent their assignment by registering another account in hope to end up in a different group. In case a participant surmounts the administrative hurdle, he nevertheless will be assigned to the same group for a certain amount of time, based on his IP-address.

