Finally, another potential problem for this trial is the expected high attrition rates at the end of online therapy and at the follow up; this attrition will also likely be higher in the waiting list control group. We will address this issue in three ways: 1) all participants must invest approximately 20 minutes for the baseline assessment, which will select more motivated participants and prevent the participation of un-motivated participants; 2) participation in the 3-month follow up assessment will be compensated by a 40 Euro incentive (an online voucher or an online charitable donation); 3) all missing values in the final data set will be imputed, a promising approach that, as shown by our Dutch colleagues, has become increasingly important in e-health research
[49].

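### The recruitment target of 267 is exactly three times 89, so the stated 80% power assumes no loss at 3 months although the protocol expects high attrition

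*Protocol article*

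**What the plan says.** The sample size section of the protocol article expects an effect "of at least 0.15 (Cohen’s f) between t0 and t2" and sizes the trial on one contrast: "we rely on the aforementioned comparison (arm 2 vs. arm 3) for sample size estimation". It then states: "A sample size of n = 89 in each study group would have 80% power (F-test, α = 5%) to detect this difference". The next sentence gives the total: "Thus, we aim to recruit a total of 267 participants". Allocation is equal across the three arms (Randomization and allocation).

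Under Aims of the trial the endpoint is fixed in time: "The primary outcome is the weekly quantity of cannabis consumed (measured in the number of standard joints per week) at the 3-month follow up".

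The last paragraph of the Discussion says "another potential problem for this trial is the expected high attrition rates at the end of online therapy and at the follow up", and adds that the loss will probably be greater on the waiting list. It offers three answers: a baseline assessment of about 20 minutes that selects motivated people, a 40 Euro incentive for the 3-month assessment, and imputation of all missing values. Elsewhere the plan describes e-mail reminders in arms 1 and 2 (Handling of study dropouts) and telephone interviews for waiting-list participants who cannot be reached online (Study interventions).

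The Background reports retention in the Australian trial that supplies the effect size: "at a 3-month follow up (54% vs. 52" per cent, intervention against control. It regards those rates as high and asks whether local access to treatment explains them.

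**The concern.** The number needed for analysis is used as the number to recruit. The effect is defined between baseline (t0) and 3 months (t2), so the power calculation needs both measurements from 89 people in each arm. Recruiting 89 per arm supplies that only if nobody is lost, and the same article says many will be. The waiting list, where it expects the greater loss, is one side of the contrast that sizes the trial.

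The stated power is what a reader will use to interpret a null result for self-help against waiting list. If it is quoted as 80% when the number observed supports less, a non-significant result will look more informative than it is. The comparison of arm 1 with arm 2 loses participants in the same way.

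This is not a detail left to a fuller document. The article itself states the power, the recruitment total and the expected attrition, and derives the second from the first without regard to the third.

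**Working it through.** **Inputs.** From the sample size section: f = 0.15, two groups (arm 2 against arm 3), α = 0.05, 89 per group, 80% power, 267 recruited. From the Background: 3-month retention of 54% and 52% in the cited trial. Assumed here: the retention rates of 90%, 80%, 75% and 70%, and the t0–t2 correlation, which the article does not give.

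**1. The recruitment total.** 3 × 89 = 267. The allowance for loss is zero.

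**2. Reproducing 89.** A repeated-measures F-test with two groups, two measurements (t0, t2) and correlation 0 has noncentrality λ = f² × N × 2, with 1 and N − 2 degrees of freedom, where N is the total in the two arms.

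- 89 per arm: N = 178, λ = 0.0225 × 178 × 2 = 8.01, power 0.804.
- 88 per arm: N = 176, λ = 7.92, power 0.799.

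The smallest N is 177, that is 89 per arm. This matches the stated figure and shows that it has no slack.

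**3. Power after loss.** Same test, same f, with 89 × retention observed per arm:

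| Retention at 3 months | Observed per arm | λ | Power |
|---|---|---|---|
| 100% | 89 | 8.01 | 0.80 |
| 90% (assumed) | 80.1 | 7.21 | 0.76 |
| 80% (assumed) | 71.2 | 6.41 | 0.71 |
| 75% (assumed) | 66.8 | 6.01 | 0.68 |
| 70% (assumed) | 62.3 | 5.61 | 0.65 |
| 54% and 52% (cited trial) | 48.1 and 46.3 | 4.25 | 0.53 |

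In the last row N = 48.06 + 46.28 = 94.34, so λ = 0.0225 × 94.34 × 2 = 4.25.

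**4. Detectable effect.** At fixed power the detectable f scales approximately with √(89 / number observed). At 53% retention this is 0.15 × √(89 / 47.2) ≈ 0.21, on the scale on which 89 per arm gives 0.15. At 80% retention it is 0.15 × √(89 / 71.2) ≈ 0.17.

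**5. For reference only: recruitment that would keep 89 observed per arm.** Dividing by retention and rounding up:

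- 80%: 89 / 0.80 → 112 per arm, 336 in total.
- 70%: 89 / 0.70 → 128 per arm, 384 in total.
- 54%: 89 / 0.54 → 165 per arm, 495 in total.
- 52%: 89 / 0.52 → 172 per arm, 516 in total.

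The German trial's attrition figures in the Background are not used, because 11.6% is there called higher than 24.7% and the two cannot be read with confidence.

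**The case against.** **The plan acts on attrition.** The 40 Euro payment depends on completing the 3-month assessment, and telephone follow-up targets the arm expected to lose most. Reminders and the baseline burden also serve retention. It would be wrong to infer that nothing in the plan raises the number observed. What stands is narrower: no measure has a stated effect, none adds participants, and the Discussion still expects high attrition.

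**Imputation keeps everyone in the analysis.** It does, but the Data analysis section imputes from baseline variables, and valid multiple imputation carries the missing 3-month information as wider standard errors. Quantity is also recorded at 1, 3 and 6 weeks (Table 1) and analysed with GEE, so people lost only at 3 months could contribute something. The table above counts only 3-month observations and may therefore somewhat overstate the loss.

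**A higher correlation could rescue power.** With a correlation of 0.5 in a within-between interaction test, 47 per arm gives about 0.82. But 89 per arm would then give 0.98, not the stated 80%. The plan cannot claim 80% at 89 and hidden slack as well. This does mean that one should not infer that 80% power is unattainable under every model; the claim holds on the plan's own terms.

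**The 52–54% is borrowed.** This is correct. It comes from another trial, and the Background itself doubts that it transfers, so retention here could be higher or lower.

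**Conclusion.** The point holds. The stated 80% power is conditional on complete 3-month data, which the plan says it does not expect. Taking the plan's premise that 89 analysed per arm gives 80%, any material loss takes power below that level, since 88 per arm already gives 0.799. The size of the shortfall depends on retention: modest at 90% (0.76), clear at 70–80% (0.65 to 0.71), and large at the cited trial's rates (0.53).

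This rests on the reconstructed test with correlation 0, on counting only 3-month observations, and on retention rates that are scenarios. Two stronger readings are tempting and are not supported. One is that the trial will have only about 53% power; the plan gives no retention rate of its own from which to say so. The other is to take a one-way F-test at f = 0.15 and quote about 0.30 after attrition. On that basis power is only 0.51 with nobody lost, so the figure mixes in the separate question of how 89 was derived.

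The omission does not by itself bias the effect estimate, and the attrition risk is openly disclosed. The error is in the stated power.

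**What to change.** In the sample size section:

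- Present 89 per arm as the number needed with 3-month data, not as the number to recruit.
- State the expected 3-month retention, by arm if the waiting list is expected to do worse, with its basis.
- Restate the power, or the detectable effect, for 267 recruited at the expected number observed, over a range of retention.

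Suitable wording would be: With 267 recruited, the expected number observed per arm at 3 months is 71 at 80% retention and 62 at 70%, giving power of about 0.71 and 0.65 for the effect that 89 per arm would detect with 80% power; at the 52–54% retention of the cited trial, power would be about 0.53.

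The test and the t0–t2 correlation behind these figures should be named so that they can be checked.

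The cost is a few sentences and a less favourable stated figure. Design, endpoint and analysis are unchanged, and no extra enrolment is required. The restatement does not itself restore 80% power; if the sponsor wishes to keep that level, the recruitment totals in the working show what it would take.

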### Baseline assessment

After providing informed consent, subjects who meet study entry criteria will create a personal and secure login and password (with automated real-time verification of the passwords’ security level) and will receive an automated e-mail notification with their access information. They will then be directed to the baseline assessment of socio-demographic characteristics and consumption patterns (see Table 
1). Participants that do not meet the inclusion and/or meet one of the exclusion criteria (see Table 
2) will receive an explanation of why they will not be permitted to participate in the study and will receive further recommendations (e.g., not to reduce their consumption of cannabis before visiting a physician and receiving any necessary treatment, etc.). A decision tree for the possible inclusion and exclusion criteria combinations will be constructed and implemented. The completion of the baseline assessment will allow participants to begin their study arm according to an automated online allocation procedure. Participants that do not fulfill the criteria can proceed with the modules from the Can Reduce web-based self-help intervention, but they will not participant in the study (i.e., there will be no assessments or compensation).

### Randomization and allocation

Once participants have completed their baseline assessment, they will be randomized by a computer program in a 1:1:1 ratio to 1 of 3 “parallel” groups, and this assignment will be automatically registered in the background database. As we offer full transparency on the three groups, we expect a certain risk that some might try to circumvent their assignment by registering another account in hope to end up in a different group. In case a participant surmounts the administrative hurdle, he nevertheless will be assigned to the same group for a certain amount of time, based on his IP-address.

### Safety

During the 6-week therapy/intervention phase, participants will have the opportunity to contact an outpatient clinic in a nearby city by telephone (lists with hours of operation, web-links, postal addresses, and telephone numbers will be provided in the appropriate language). Additionally, a medical advisory and emergency list that is based on the web-based treatment guidelines of the Federation of Swiss Psychologists
[42] (in line with the HONcode
[43], a code of ethics for medical information on the Internet) will be provided for cases of emergency. This list will always be accessible to participants in all study arms before, during, and after study participation regardless of whether the participants withdraw from the study. This list will include phone numbers for emergency help lines and the contact information of the study team and the webmaster.

### Experience, training and supervision of chat counselors

To ensure that chat counseling sessions in study arm one are conducted in the same MI style and cover all relevant points, the chat counselors will be trained MI counselors with at least one year of experience in treating cannabis-abusing patients who will follow a check list in each counseling session. Two senior psychiatrists with extended face-to-face and web-based addiction counseling/therapy experience will train and supervise junior counselors. Specific addiction chat counseling quality standards will be developed and implemented for this study based on the EQUS treatment quality standards
[44] and extended to Swiss national addiction counseling quality standards.

### Trial flow

Figure 
1 provides an overview of the trial flow. If a participant successfully completes the baseline assessment (t0), he or she will be introduced step-by-step into the corresponding study arm, invited to participate in part one (study arms 1 and 2), or informed that they will be provided access to the web-based self-help within approximately 12 weeks (waiting list condition). Participant in the intervention arms 1 and 2 will receive automated e-mail notifications to login and enter their cannabis consumption frequency and quantity into their consumption diary every week. Access to all modules will be unrestricted from day one. However, the participants will be encouraged to complete all key modules (modules 1–4) in order, to complete at least two further modules chosen from modules 5 to 8 and to repeat any modules they feel they need or that they perceived as helpful within the 6 weeks of duration of study arms 1 and 2.

Six weeks after the baseline assessment, participants will again be invited by e-mail to login and complete the final study assessment (t1). Participants will be invited to complete the follow up assessment (t2) by an e-mail message that will be sent 3 months after t0; this message will inform the participants that completion of the entire 3-month follow up assessment will be compensated with 40 Euro (via an online voucher or an online charitable donation).

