The additional two chat counseling sessions in study arm one will apply support regarding behavioral change according to MI, discuss the modules of the web-based self-help part based on MI and CBT, review the development of the consumption diary and will be structured as follows:

• Chat session 1: Starting point and objective agreement

• Personalized feedback according to baseline assessment of cannabis related physical and mental health risks

• Review of successful strategies of change related to topics other than cannabis

• Imagining daily routines after cannabis cessation; exploration of aims to live without, and the dissonances of, cannabis use; mobilization of social support with the invitation for a relevant third person to join chat session 2

• Agreeing on a cannabis use objective expressed in tangible numbers (e.g., a maximum of two standard joints per week, complete cannabis abstinence etc.)

• Chat session 2: Experience exchange and consolidation

• Experience exchange regarding the agreed-upon objective since the starting point

• Review of the patterns of the consumption diary goals and achievements

• Review and consolidation of web-based self-help modules

• Experience and improvement of social support

• Revising objectives

• Saving strategies for long-term success

The web-based self-help intervention and the subsequent tailored chat counseling aim to reduce cannabis use. However, those participants who seek cannabis abstinence will also be encouraged to make step-by-step reductions until full abstinence has been reached. The maintenance of abstinence from one day to the next, as is recommended by the content of tobacco prevention websites
[31], will not be advised for safety reasons (e.g. to avoid possible severe withdrawal symptoms).

Participants randomized to the waiting list will have the opportunity to participate in the web-based self-help intervention 3 month after registration. Follow up measures for those participants will be assessed online or by telephone interviews for those participants who cannot be reached online at the 3 month follow up.

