^1)^ Additional retrospective cost-relevant information directly or indirectly related to cannabis use will be collected by the CLAMES to conduct cost-effectiveness and cost-utility analyses.

^2)^ 7-day point prevalences of the quantity (in common standard joints) and frequency (the number of days on which cannabis is used) of cannabis use will be derived from the consumption diary assessed daily using data from the last 7 days.

Moreover, the following secondary outcome instruments will be applied: 1) cannabis consumption days per week according to the consumption diary; 2) the Cannabis Use Disorders Identification Test (CUDIT), which is a 10-item questionnaire
[33] that was constructed by adapting the Alcohol Use Disorders Identification Test (AUDIT
[34]). To cover the length of the trial length, this instrument will be adapted to focus on the last 3 months in its planned assessments (baseline and 3-month follow up); 3) The Severity of Dependence Scale (SDS), which is a 5-item questionnaire that measures the severity of cannabis dependence. Each of the five items is scored on a 4-point scale (0–3). The total score is obtained through the addition of the ratings on all 5 items. High scores indicate high levels of dependency
[35]; 4) The Cannabis Withdrawal Scale (CWS)
[36], which is a 26-item questionnaire containing statements that describe cannabis withdrawal symptoms within the last 24 hours on 11-point scales (0–10); 5) The Cannabis Craving Symptoms questionnaire (CCS-7), which is a 7-item questionnaire
[37] derived from the Marijuana Craving Questionnaire
[38]. Each item is rated on a 7-point-scale (1–7); 6) the “Fragebogen Substanzanamnese” (FDA), which is a questionnaire that ascertains the number of years of consumption over the lifetime, the past month’s consumption, and the manner of consumption for DSM-IV/ICD-10 substances of abuse. This measure was derived from the Europe ASI
[39]; 7) the short version of the Mental Health Inventory (MHI-5)

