Some participants may want to reduce their cannabis use only marginally and might reach their aims in the first weeks of the intervention, which might result in discontinuation of participation in the online self-help intervention. Therefore, we will recommend that participants reduce their cannabis by at least 20 to 30 percent in the first week of the intervention and continue with this strategy in subsequent weeks if they succeed. For participants who do not succeed, we will recommend that they create more modest goals until their final aim is received. Participants receiving chat counseling will additionally be motivated by their counselors to avoid setting their goals too low.

During the online implementation of the consumption diary of the web-based self-help intervention, pilot participants stressed the importance of the definition of common standard joints as the most appropriate measure for the consumption diary. On the one hand, the established cannabis meter pictures from the global drug survey website facilitated the pilot participants’ entry of their cannabis use, and, on the other hand, they felt more motivated by a tailored photograph than a written instruction. In our opinion, this is the most effective method to collect appropriate quantity measures, especially from cannabis users who use cannabis several times a day. However, as this is the first time this kind of quantity measure will be used in a randomized controlled trial, we will also rely on the number of days per week that cannabis is used.

One specific problem involves the online implementation of informed consent. As in previous research
[21], we will rely on participants to click on a field on the informed consent page and submit the consent with a submission button. Thus, we must trust that the participants have read and understood the study information and that they are at least 18 years old. However, as we followed the recommendations of
[47] and
[48] regarding the best implantation of online informed consent procedures, we expect that the participants will read the study information in full and provide informed consent.

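### The article gives two different times for waiting-list access, and neither puts the primary assessment before access, so some controls' 7-day outcome may be reported after they have the programme

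*Protocol article*

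**What the plan says.** **When controls get the programme.** In Trial flow, participants in arm 3 are "informed that they will be provided access to the web-based self-help within approximately 12 weeks (waiting list condition". In Study interventions, they "will have the opportunity to participate in the web-based self-help intervention 3 month after registration".

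**When the primary outcome is taken.** The aims section states: "The primary outcome is the weekly quantity of cannabis consumed (measured in the number of standard joints per week) at the 3-month follow up". Participants are invited to t2 "by an e-mail message that will be sent 3 months after t0" (Trial flow). That is the date of the invitation, not of the answer. For the waiting list, Study interventions adds that follow-up will be "assessed online or by telephone interviews for those participants who cannot be reached online at the 3 month follow up". No latest date is given.

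**What the outcome covers.** The footnote to Table 1 says that the quantity and frequency measures "will be derived from the consumption diary assessed daily using data from the last 7 days".

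**What access brings.** For arms 1 and 2, Trial flow says: "Access to all modules will be unrestricted from day one". The Discussion adds: "we will recommend that participants reduce their cannabis by at least 20 to 30 percent in the first week of the intervention".

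**The concern.** Hypotheses 1 and 2 compare each active arm with an untreated waiting list, and the sample size rests on arm 2 against arm 3. Both need a control value at t2 that was formed without the programme. The stated timings do not secure this. Access is due at about the time of the t2 invitation or some days earlier, while the answer comes on or after the invitation. The outcome covers only one week, so a few days' difference in order can decide whether that week is untreated.

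If exposed controls cut down, the difference from arms 1 and 2 shrinks. The planned analysis would not repair this. A t2 value given after access is observed, so multiple imputation leaves it alone, and the cross-check on the non-imputed data contains the same value. Hypothesis 3 compares arm 1 with arm 2 and is not affected.

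**Working it through.** **Inputs**

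- Access day A, Trial flow, read literally: 12 × 7 = 84 days after t0.
- Access day A, Study interventions: 3 months after registration. The Baseline assessment section has participants create a login and then go on to baseline, and the Discussion puts baseline at about 20 minutes. I therefore take registration and t0 as the same day, so A falls on the invitation day.
- Invitation day I: 3 calendar months after t0, which is 89 to 92 days. For example, 1 February to 1 May in a non-leap year is 28 + 31 + 30 = 89, and 1 March to 1 June is 31 + 30 + 31 = 92.
- Look-back: 7 days, assumed to end on the day when t2 is answered.
- Delay s: days from invitation to answer. The article gives no value, so a range is shown.

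**Overlap.** Days of the window that fall after access = max(0, min(7, I + s − A)).

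| Delay s | A = 84, I = 89 | A = 84, I = 92 | A = I |
|---|---|---|---|
| 0 | 5 | 7 (8, capped) | 0 |
| 2 | 7 | 7 (10, capped) | 2 |
| 7 | 7 (12, capped) | 7 (15, capped) | 7 |
| 14 | 7 (19, capped) | 7 (22, capped) | 7 (14, capped) |

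Under a literal 12 weeks, most or all of the window lies after access even for a same-day answer. Under the 3-month statement, a prompt answer has no overlap, but an answer 7 or more days late lies wholly after access.

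**Looser reading of 12 weeks.** If the approximate figure stands for 13 weeks, A = 13 × 7 = 91. A same-day answer then gives 0 days of overlap for I = 89 and 1 day for I = 92, close to the 3-month column.

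**Consequence for power, as an illustration only.** The planned 89 per arm is reproduced by a repeated-measures F-test with 2 groups, 2 measurements, f = 0.15 and a correlation of 0. This gives a total of 177, rounded up to 178 = 2 × 89, and 3 × 89 = 267. The correlation is not stated in the article; that is a separate matter. Take 80% power as planned and suppose that exposure shrinks the arm 2 against arm 3 difference by a fraction k. In a simple two-group comparison, power is then Φ[(1 − k)(1.960 + 0.842) − 1.960]:

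- k = 0.10: Φ(0.562) = 71%
- k = 0.25: Φ(0.14) = 56%
- k = 0.50: Φ(−0.56) = 29%

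The values of k are assumed. Nothing in the article allows k to be estimated.

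**The case against.** **The 12-week figure is approximate.** It reports what participants are told and may be a rounded form of 3 months. A reader might infer that every control has the programme 5 to 8 days before the invitation (89 − 84 to 92 − 84). The text does not support that: it needs an approximate figure to be read as exactly day 84, and under the other statement the gap is about zero. This objection stands. What it leaves is the late or telephone responder, for whom the order is unprotected under either statement.

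**The order may be fixed elsewhere.** Figure 1 is the trial flowchart and is not shown, and an article may leave the release of accounts to the full protocol. This also stands, so the absence of an ordering rule can be reported only for the visible text. The two written access times still differ and need reconciling.

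**The size is unknown.** A reader might infer from the first-week advice that exposed controls would use 20 to 30% less, or 6.7 to 10% less on average if one third took it up (1/3 × 20 to 30%). The article supports neither figure. Both need immediate uptake, full compliance and a window wholly after access, and the Discussion itself expects that some participants will not reach the advised reduction. Access is also not use: a control may have an open account and not log in.

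**The bias is conservative.** It would work against hypotheses 1 and 2 rather than create a false benefit. That is true, but a diluted contrast can still hide a real effect.

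**Conclusion.** The point holds in a limited form. The article states two access times that do not agree. Under both, access can be open by the time a control completes t2, and no visible text places t2 first. The 7-day window makes the outcome sensitive to this order.

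The extent runs from about 0 of 7 days (3-month access, same-day answer) to 5 to 7 of 7 days (literal 12 weeks, same-day answer), and to the whole window for an answer 7 or more days late under either statement. This rests on registration and t0 falling together and on the look-back ending on the day of the answer. If the window were anchored to the invitation date instead, overlap would not grow with delay. The likely direction is towards no effect for hypotheses 1 and 2, provided that exposed controls cut down. The size cannot be derived from the article. The point is worth correcting because the correction is cheap and the untreated value cannot be recovered afterwards; it does not show that the control arm will in fact be contaminated.

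**What to change.** 1. Reconcile Study interventions and Trial flow to one statement of waiting-list access, and check that Figure 1 and the participant information agree with it.
2. Keep t2 at 3 months after t0 in all arms, and state how long the t2 window stays open, telephone interviews included.
3. Unlock each waiting-list account only once that participant's t2 is submitted or the stated window has closed. For assessments completed within the window, the overlap is then 0 days.
4. Record the dates of access, first log-in and t2 completion for every control, so that any remaining overlap can be reported.

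Do not add a sensitivity analysis that leaves out controls who logged in before answering t2. It would drop participants for post-randomisation behaviour in one arm only, probably the more motivated ones, and would sit badly with the intention-to-treat plan.

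The cost is one condition in the software, a few lines of text and a short delay in access for controls who answer t2 late. Because the window closes on a stated date, access is not withheld indefinitely from those who never answer.
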